### Gross Motor Function Classification System (GMFCS)

The GMFCS for children with CP classifies how children perform self-initiated movements based on sitting (truncal control) and walking across a five levels [72]. Construct validity has been obtained with a correlation between the GMFCS and the Gross Motor Function Measure (GMFM) of *r =* 0.91 [72]. The measure also has good inter observer reliability between professionals and professionals and parents in children with CP [73]. This classification measure has not been validated for use with children who have an ABI however it is expected that all children in the sample will be equivalent to a GMFCS I (walks without limitations) or II (walks with limitations). Children will be classified by a physiotherapist.

### Manual Abilities Classification System (MACS)

The MACS is a five level classification of how well children with CP use their hands to handle objects in day-to-day activities [63]. The MACS has reported construct validity and excellent inter-rater reliability (Intra-class correlation coefficients [ICC] = 0.97 between therapists and ICC = 0.96 between therapists and parents) for children with CP [74]. This scale has not been validated for children with an ABI however, it is expected that all children included in this study will be equivalent to MACS level I (able to handle objects easily and successfully), level II (able to handle most objects but with somewhat reduced quality and/or speed of achievement so that alternate ways of performance might be used) or level III (handles objects with difficulty; needs help to prepare and/or modify activities). Children will be classified by an occupational therapist.

### Edinburgh Handedness Inventory

During baseline assessments, hand dominance will be assessed using the The Edinburgh Handedness Inventory [75]. The Edinburgh Handedness Inventory questionnaire consists of 10 items regarding hand preference (right or left) in performing a number of everyday tasks requiring one (writing, drawing, throwing and using scissors) or two (e.g. using a broom or opening a box) hands. A laterality quotient is calculated using the following formula: laterality quotient = (right hand – left hand/(right hand + left hand)*100).

### Passive Range of Motion (ROM)

Passive ROM for the unimpaired and impaired side will be assessed by the same occupational therapist (UL) and physiotherapists (LL) at baseline only to determine any relevant impairments (e.g. joint contractures) which may limit access to the program and inform participation in the study.

### Sensory measures

Three different descriptive, sensory measures will be obtained from participants at baseline by an occupational therapist:I.Stereognosis will be assessed on the non-dominant and dominant hands using the approach described by Feys [76]. Three familiar objects (teaspoon, key and peg) and six similar matched objects (safety pin and paperclip; pen and pencil; coin and button) will be used. With vision occluded, participants will be presented with each item. If a participant is unable to grasp, manipulate or release an object the occupational therapist will assist the participant and move the object for them within their hand. A corresponding set of items will be used to allow participants to identify the object in order to minimise any errors due to incorrect naming of the object. Scores range on a scale from 0–9, where participants scoring below 9, will be considered to have impaired stereognosis [77].II.Moving two point discrimination (M2PD) will be measured using the Disk-criminator® (Baltimore, Maryland) on both the non-dominant and dominant hands. Either one or two points will be randomly applied in continuous moving firm contact longitudinally to the pulp of the index finger with vision occluded [78]. The minimum distance participants can usually distinguish between two discrete points, ranges from 2mm (normal) to 15 mm (poor) [79].III.Texture Tactile Perception will be tested using the AsTex Perspex board that displays tactile gratings of reducing tactile discrimination index [80]. Starting at the “rough” end of the board, movement of the participant’s index finger, then thumb, then fifth finger will be guided by the examiner along the board at a constant speed in a standardised manner. Participants will be instructed to stop immediately when the board feels smooth (gratings become too close together to determine their separation). Each point will be recorded, with the final outcome the average of three trials for each digit. The average scores will be converted to the tactile discrimination index for each finger using the chart available with the test kit.

### Mirror movements

The presence of mirror movements will be assessed (by an occupational therapist) and scored on the side of the body unintentionally performing the movement during three unimanual UL tasks: (i) rapid tapping of the index finger on the distal thumb, (ii) alternating supination and pronation of the forearm and (iii) repetitive alternate touching of each fingertip to the tip of the thumb of the same hand, in order. Participants will be scored on a four point scale ranging from no clearly imitative movements, to movement equal to that of the intended hand. Possible total score range is from 0–12 [81].

### Grip strength

Grip strength will be measured using a hand held dynamometer (Smedley®, Scientific Instruments Co Ltd) by an occupational therapist. Grip strength will be measured for three attempts on each UL (kilograms force, Kgf) according to the guidelines of the American Society of Hand Therapists [82]. The mean of the three attempts will be used to compare limbs and to evaluate changes over time.

### Anthropometric data

Height will be measured to the nearest 0.5 cm while the participant is standing with his or her back against a wall with a ruler. Body Mass Index (BMI) will be collected at baseline only. This will be used to convert activity capacity tests into referenced percentiles.

### Wechsler Intelligence Scale for Children–Fourth Edition (WISC-IV)

Overall level of cognitive intellectual functioning will be assessed using the WISC-IV [65]. The WISC-IV consists of ten subtests that make up the four indices of verbal comprehension (VCI), perceptual reasoning (PRI), working memory (WM), and processing speed (PSI). A full scale intelligence quotient (FSIQ) score can be calculated from these index scores. The VCI index is made up of the Vocabulary, Comprehension and Similarities subtests. The Vocabulary subtest assesses knowledge of word meaning and will require participants to name pictures or provide spoken definitions of words (e.g., “what is a bicycle?”). The Comprehension subtest measures verbal reasoning and conceptualisation and demonstrates practical information. The Similarities subtest assesses verbal abstraction and reasoning and will require participants to describe how two words are similar (e.g., “how are anger and joy alike”). The subtests of Block Design, Picture Concepts and Matrix Reasoning make up the PRI index. Block design will require participants to construct abstract visual designs using a set of red-and-white three dimensional blocks within a specified time period. Picture Concepts is designed to measure nonverbal abstract, categorical reasoning ability. For Matrix Reasoning, participants will be shown an array of visual designs with one missing square. They will be required to use their non-verbal abstract reasoning and problem solving skills in order to select the correct picture from an array of five options that fits into the missing space of a visual design. The WMI index is made up of the Digit Span and Letter-number sequencing subtest. For the Digit Span subtest, participants will be required to repeat a number of verbally presented digits in both the forward and reverse order. The Letter-number sequencing subtest will require participants to sequence letters and numbers in order which involves sequencing, mental manipulation, attention and short term auditory memory. Finally, the PRI index is made up of the Coding and Symbol Search subtests. For the Coding subtest, participants will need to match up abstract symbols with numbers from a key and for Symbol Search, participants will be required to detect the presence of one or more symbols in a sequence of five. These subtests have a two-minute time limit and therefore require participants to work as quickly as possible without making mistakes [65].

Raw scores from the subtests can be converted into scaled scores with a mean of 10 and standard deviation (SD) of three using age and gender appropriate normative data. Index scores can be converted into composite or scaled scores with a mean of 100 and SD of 15. The VCI, PRI and WMI and FSIQ index scores of the WISC-IV demonstrate very high levels of internal consistency (α > 0.90). The PSI index has high internal consistency (α = 0.80-0.89) [65].

## Neurovascular measures

### Whole-brain fMRI studies

All participants will be checked for 3T MRI safety including no metal implants or ventriculoperitoneal shunts. Participants will be prepared in the mock MRI scanner prior to the real scan to familiarise them with the image procedure and minimise the potential for psychological distress.

Functional imaging at 3T on a Siemens MAGNETOM Trio MRI scanner will be conducted on the research dedicated scanner at The University of Queensland, Centre for Advanced Imaging (CAI), Brisbane, Australia. Published methods will be utilised for conducting serial functional MRI (fMRI) studies including preparation in a mock MRI scanner and assessing activation during a range of tasks as outlined below. Two of three tasks will be performed, depending on age and motor abilities:(i)All participants will perform a simple wrist flexion/extension movement task in a two-condition block design, visually cued via instructions projected on a screen. The baseline condition is no movement (rest). A recording of a metronome at two hertz will provide an auditory cue for the rate of movement. Participants will be required to flex and extend the wrists of each hand one at a time, in time with metronome and lie still with no movement during the baseline blocks. The task and rest periods are 30 s with the activation cycle repeated four times. The movements performed in the scanner will be rated for speed, ROM, ability to isolate the movement and presence of mirror movements in the contralateral hand. If there is task-correlated breath-holding, the task will be repeated.(ii)Older participants and those with sufficient fine control in the least impaired hand will also perform a complex movement sequencing task, aimed at examining function in higher motor areas and basal ganglia circuits. In this task, visual cues will indicate a sequence of three button-presses to perform (e.g. 132; sequence condition), or three simple repetitive presses with the index finger only (e.g. 111; simple condition). The task will be run in blocked design, with 20 s of simple, 20 s of sequence, and 20 s rest blocks in counterbalanced order for a total scan duration of six minutes.(iii)For examination of visuo-spatial processing and spatial working memory, a mental rotation task will be used [83]. For each trial, participants will be presented with a single target stimulus above fixation and two-test stimuli below, on the visual display. Participants will be required to indicate by button-press which test stimulus matches the target. Mental rotation stimuli are Shepard–Metzler three-dimensional cube objects, with target and test stimuli differing by 30° or 60° rotation (two dimensional rotation only), as used previously in children of the same age range [83]. In a baseline condition, participants must indicate which of two spatial Fourier-transformed ‘noise’ patches is the best visual match to the target. Stimuli are presented for 10 s with one second inter-stimulus interval. Groups of three baseline trials alternating with three rotation trials (forming 33 s blocks) are presented in 12 blocks over a total scan duration of six minutes and 36 s. The mental rotation task is similar to matching puzzle pieces, which some children may find interesting. The mental rotation task has been performed in paediatric populations with Attention Deficit Hyperactivity Disorder (ADHD) [83]. As the mental rotation task is quite different to the current battery of occupational therapy and neuropsychological tests, children will perform the task both inside and outside the scanner to compare performance and account for practice effects. An additional five minutes of resting-state fMRI will also be collected for analysis of FC. Tasks performed prior to resting-state fMRI can influence FC so the resting-state data will be collected after the motor paradigms [84].

For all tasks, fMRI will be acquired using a BOLD acquisition sequence (Gradient-recalled-echo [GRE] Echo-Planar Imaging [EPI], Repetition Time [RT] = 3.0 s, Echo Time [ET] = 30 milliseconds, flip angle = 850, slice thickness = 3 mm, Field of View [FOV] =216 mm, 44 slices, 72 × 72 matrix yielding an in-plane resolution of 3.0 mm × 3.0 mm). A single set of T2-weighted anatomical, FLAIR and 3D T1 (MPRAGE 1mm isotropic resolution) volumes will also be collected. Functional MRI image processing, analysis and visualisation will be performed using SPM software (Welcome Department of Imaging Neuroscience, London, UK).

### Diffusion imaging acquisition and white matter fibre tracking

Diffusion-weighted images will be acquired using a twice-refocused single-shot EPI sequence (64 directions, B-value = 3000 s per millimetre squared (s/mm^2^), contiguous slices with whole-brain coverage at 2.2 mm isotropic resolution, acquisition time approximately 10 min). White-matter tractography will be undertaken in a manner robust to crossing fibres, using constrained spherical deconvolution (CSD) and probabilistic streamlines using MRtrix software [85–87].

To improve the understanding of cortical plasticity post-intervention, cortical reorganisation will be investigated using a combined fMRI-probabilistic tractography approach. White matter connectivity maps will be produced using MRtrix by seeding every brain voxel and using regions of corticomotor activation generated post-intervention as target masks for the tracking algorithm. This will enable identification of all cortical regions, which have white matter tracts that directly project into corticomotor regions exhibiting plasticity as a result of the motor training paradigms. By comparing connectivity maps pre and post-intervention (registered within the same image space), this strategy enables both an anatomical view of cortical reorganisation and quantitatively analyses altered connectivity by measuring the number of streamlines connecting two cortical regions, corrected for brain size. The basis of this strategy has recently been published in Neuroimage [88]. It is hypothesised that increased intrahemispheric and interhemispheric connectivity showing recruitment of additional corticomotor areas will directly correlate with improved motor function [88]. The HARDI paradigm for this cohort of children is the same as previously conducted at CAI in the Mitii™ CP and CoMBIT protocol studies [89, 90].

Nine typically developing children will also be recruited as a reference sample for the neuroimaging studies. Children will be recruited through staff newsletters and from other studies within the centre. Five children will complete all tasks involved for fMRI, sMRI and dMRI. Four children will only complete sMRI and mental rotation tasks.

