## Statistical analysis

### Sample size

The primary basis for sample size calculation for this study is adequate power (80 %) to detect a clinically important difference for the comparison between the functional effects of Mitii™ (as measured on the AMPS and rep_max_ of functional strength exercises) and usual care at the primary endpoint (20 weeks). This study examines a continuous response variable from matched pairs, waitlist control and immediate-intervention participants with one waitlist control per immediate intervention participant.

In a previous study of Mitii™ in children with unilateral CP (n = 102) the response within each group was normally distributed with SD 0.40 on the AMPS process subscales [49]. To detect a real changes in ADL processing abilities (0.30 units of greater) [92] between groups with 80 % power and α = 0.05, 29 children from each group are required to complete 20 week follow-up assessments.

For rep_max_ of functional strength exercises in a previous reliability study, the response within each subject group was normally distributed with a SD of five sit-to-stand repetitions [93]. If the clinically important difference between groups is four repetitions we will need 26 children from each group to complete 20 week follow-up assessments with, α = 0.05 [47].

Based on a previous RCT using 3T fMRI there were activation in the representative cortex for motor studies with good signal to noise ratio. Participant numbers will allow for some loss of information due to participant refusal (10 %) and scans where motion is a confounder (10 %). To detect fMRI changes between baseline to follow-up assessment (20 weeks) with 80 % power and a SD of 0.65, we will require 39 participants. If the supplementary motor area (SMA) is considered, given coefficients of variation (COV) for control subjects performing motor tasks (COV of 11 % in PM1 and 35 % in SMA, and activation signal of 1.5 %, we will be able to detect differences in percentage activation levels over time as small as 0.47.

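### Tractography target regions are chosen from post-intervention activation alone, yet are described as plasticity caused by training

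*Protocol article*

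**What the plan says.** The section on diffusion imaging acquisition and white matter fibre tracking describes a combined fMRI and tractography method. Connectivity maps are produced by seeding the whole brain and "using regions of corticomotor activation generated post-intervention as target masks for the tracking algorithm". The section then says that this identifies the cortical areas whose tracts "directly project into corticomotor regions exhibiting plasticity as a result of the motor training paradigms". A comparison over time enters only after the targets are set: "By comparing connectivity maps pre and post-intervention (registered within the same image space"), with streamline counts corrected for brain size. The hypothesis given there is of increased connectivity that reflects recruitment of further corticomotor areas.

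The activation comes from the tasks in the section on whole-brain fMRI studies. The task common to every child is movement set against rest: "All participants will perform a simple wrist flexion/extension movement task in a two-condition block design".

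Three other places bear on the point:

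- Secondary hypotheses: neurovascular change on functional MRI is listed among the gains expected relative to usual care.
- Study procedure: for the waitlist arm, the 20-week visit (T1) is a second baseline. Its post-intervention visit is T2, at 40 weeks.
- Sample size: control-subject motor activation is given as "COV of 11 % in PM1 and 35 % in SMA, and activation signal of 1.5" per cent.

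**The concern.** The description makes two steps that the data entering the mask cannot support. The first is from activation at one visit to change: the contrast's reference condition is rest in the same session, not the earlier scan. The second is from change to a training effect: no usual-care information enters the definition. Moving the wrist activates motor cortex in trained and untrained children alike.

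Two further problems follow. Areas active only at the first scan are not targets, so this analysis does not follow connections to areas that drop out, while the stated hypothesis is about areas being added. And a mask defined by the post-intervention scan does not exist for waitlist children at the 20-week endpoint, so the randomised comparison cannot be made with it as written.

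The mechanism of training is the trial's stated secondary aim. A report that followed this wording could present normal task activation as evidence of training-induced reorganisation.

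**Working it through.** **Step 1. Reproduce the protocol's nearest figure.** The mask rule carries no figure. The Sample size section says "we will be able to detect differences in percentage activation levels over time as small as 0.47" for the supplementary motor area (SMA).

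- SD = 0.35 × 1.5 = 0.525.
- Detectable difference = (1.960 + 0.842) × SD × √(2/n), with two-sided α = 0.05 assumed and 39 children split as n = 19.5 per group: 2.802 × 0.525 × √(2/19.5) = 0.471. This matches 0.47.
- A one-sample paired formula with n = 39 gives 2.802 × 0.525 / √39 = 0.236, which does not match.
- SD 0.65 with 30 per arm also gives 0.470, so the SD behind the figure is not certain.

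Both matches use a two-sample formula. That fits scanning of both arms but does not prove it: one group of 19.5 measured twice, with the visits treated as independent, gives the same number. The other statement there, "with 80 % power and a SD of 0.65, we will require 39 participants", names no effect size and cannot be checked.

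**Step 2. Share of children with no training effect whose region would enter the mask.** Assumptions: activation is normal with mean 1.5%, the COV is between subjects, and children with ABI activate like control subjects. SD is 0.11 × 1.5 = 0.165 in PM1 and 0.525 in SMA. The share is P(activation > c) = 1 − Φ((c − 1.5)/SD). The cut-offs c are assumed, since the protocol states none.

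| Cut-off c | PM1 | SMA |
|---|---|---|
| 0% | 100% | 99.8% |
| 0.47% | 100% | 97.5% |
| 0.75% | 100% | 92.3% |
| 1.0% | 99.9% | 83.0% |

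**Step 3. Add scan noise.** Suppose instead that a region counts as active when signal divided by its single-scan standard error (SE) exceeds 3.09 (p < 0.001), with true activation the same at both visits. The SE values are assumed. Simulation gives:

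| SE | PM1 | SMA |
|---|---|---|
| 0.15 | 100% | 97% |
| 0.30 | 95% | 83% |
| 0.40 | 73% | 66% |
| 0.50 | 47% | 48% |

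**Step 4. Compare with a rule that requires change.** Under the same model, a post-minus-pre rule labels only its own test level: 0.1% at p < 0.001, or 5% at one-sided 0.05. This removes the single-visit problem only. Growth or task repetition over 20 weeks would still pass a within-arm change rule, so the waitlist arm is needed to attribute change to training.

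**Step 5. Look for a repair elsewhere in the protocol.**

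- Blinding: a qualitative rating of change over time, not linked to the masks.
- Statistical analysis: two-group comparisons at 20 weeks with baseline adjustment. This governs how outcomes are compared, not how the mask is built or named.
- Structural parcellation and Connectome construction: a separate whole-brain analysis on anatomical regions, with no activation mask.
- Statistical analysis of the brain network: fractional anisotropy compared between participant groups for each connection, adjusted for age.

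None of these changes the mask or its description.

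**The case against.** The strongest reply is that the mask is not a decision rule. It tells the tracking algorithm where streamlines must end; the quantity analysed is the streamline count, which is compared before and after and can fall as well as rise. No outcome or test counts regions labelled plastic, so the shares above are not false-positive rates of any planned test. This stands, and no bias in the streamline counts themselves has been computed.

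It can also be said that the connectome analysis already uses anatomically fixed regions, that the general analysis section plans comparisons between arms, and that details of contrast and threshold may sit in the published method the section cites. The first two are true but concern other analyses or the general model. As to the third, unseen detail may narrow the mask, but the article itself commits to the post-intervention scan as the source and to the causal reading. Activation generated after the intervention might be meant as newly arising activation, but no contrast is given that would make it so.

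Three stronger readings are tempting and are not supported:

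- That nearly every child would be mislabelled. This depends on cut-offs and noise levels the protocol does not give; with noisy scans the share is about half.
- That the tractography has no change input or cannot show any loss. Counts into the retained targets can decline, and the connectome covers every pair of nodes.
- That every pre-post difference will be credited to Mitii. The planned two-group comparisons argue against assuming this.

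**Conclusion.** The point holds for the mask and its label. The target regions are set by activation at one visit in one treatment state, and the protocol calls them the product of training. Task-active motor cortex would receive that description with no training effect. Under the protocol's control-subject inputs the share affected is between about 47% and nearly 100%, conditional on normality, a between-subject COV, control-like activation in children with ABI, and an assumed cut-off or scan error. The qualitative conclusion needs none of these: it follows from the movement-versus-rest contrast and the absence of any earlier or control scan in the definition. The omission of areas active only before training, and the lack of a defined mask for waitlist children at 20 weeks, follow directly from the text.

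This is a secondary, mechanistic analysis in an imaging subset. It should be corrected, but the primary outcomes do not depend on it.

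**What to change.** - Define the target mask by visit rather than by treatment state: either the union of T0 and T1 activation, or an anatomical region fixed in advance, for example from the protocol's own structural parcellation. Apply the same mask to both scans in both arms.
- Compare streamline counts between arms at T1 adjusted for T0, as the general analysis section already does for outcomes.
- Speak of plasticity resulting from training only where the T0-to-T1 change differs between arms.
- State whether waitlist children in the imaging subset are scanned at both T0 and T1. The Sample size section implies imaging from baseline to 20 weeks without naming the arms, and the abstract says only that a subset is scanned before and after intervention. If waitlist children lack either scan, keep the time-symmetric mask and drop the causal wording.

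If both arms are scanned at both visits, this changes only the image-analysis text and the processing. The price is precision: a between-arm contrast is less precise than a pre-post comparison within one arm.
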